### Analysis plan—primary and secondary outcomes

The primary analysis will use the intent to treat approach. All randomized participants eligible to meet a study outcome will be analyzed according to the arm they were assigned to evaluate the efficacy of the navigator intervention. This analysis will include those whose outcome cannot be ascertained at follow-up. We will assume conservatively that participants who cannot be found by study personnel and who do not have data available in the medical record were not linked to care.

The first phase of the analysis will evaluate the success of randomization in distributing baseline characteristics evenly between the intervention and the usual care arms. Baseline characteristics that are not balanced across the study arms will be advanced into regression models, evaluating the efficacy of the intervention, to address possible confounding. Characteristics that are balanced but that have an association with the outcome will also be advanced to final models to reduce error variance. To evaluate the hypothesis that the intervention will improve linkage rates, we will use adjusted logistic regression modeling to determine successful linkage to care. Secondary outcomes will be analyzed in a similar fashion.

We will conduct a series of hypothesis-generating secondary analyses to examine the potential impact of several predisposing (age, gender), enabling (social support, self-efficacy), and perceived need factors (reason for HIV testing) from the Andersen model
[17,18] as moderators and mediators of the intervention. We will build several logistic regression models, one at a time, with interaction between study arm and age, gender, social support scale and reason for HIV testing, due to capped sample size. These analyses will demonstrate whether the intervention is differentially more efficacious in particular patient subgroups. If the intervention is efficacious in improving linkage to care, we will perform additional analyses that attempt to identify the mechanism of intervention effect, for example, whether the intervention improves social support and self-efficacy, and whether these improvements enhance linkage to care. This hypothesis-generating analysis will be valuable for determining whether future studies of this intervention should target particular patient subgroups and whether certain effects of the intervention (e.g. improvement in self-efficacy) are especially integral to intervention efficacy.

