### Randomization

After completing the baseline questionnaire, enrolled participants were randomized, prior to HIV testing, to the intervention or the usual care arm. Randomization was stratified by site and gender, with blocks of varying length. Randomization assignments were created by the Boston-based Data Coordinating Center. A randomization table that was inaccessible to the South African research assistants was embedded in a Handheld Assisted Patient Interview (HAPI) device and provided randomization assignments for consecutive study numbers.

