### Sample size

Based on our prior work at McCord and St. Mary’s Hospitals, we estimated the HIV prevalence to be 35% among enrollees, with approximately 20% of HIV-infected enrollees co-infected with TB
[23-25]. Based on the ART-eligibility criteria at the start of the study, we anticipated that 22% of enrolled participants would be eligible to meet a primary outcome. Based on our prior work, we expected 35% of HIV infected/TB negative patients in the control group to achieve the primary outcome. Our power considerations were based on the assumption that the intervention will affect HIV and TB treatment outcomes similarly, which we thought reasonable given the lack of data on linkage to care interventions that distinguish between these groups. The study was originally powered (90%) to detect a 27% increase in linkage to care in the intervention arm. We planned to enroll 4,745 participants in total, with 1,661 HIV-infected individuals eligible to reach the study outcome.

In June 2012, the McCord Hospital HIV clinic closed due to the conclusion of PEPfAR funding, thus we ceased enrollment at the McCord outpatient department because participants could no longer meet the primary outcome at the enrollment site. We redeployed the McCord team to Mariannridge Clinic beginning in August 2012. Additionally, with the approval of the trial DSMB, we used actual trial data on HIV prevalence and the proportion who receive a CD4 count to refine our sample size requirements. The updated sample size called for an additional 149 patients, for a new total of 4,894 participants, 1,714 of whom are HIV-infected.

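### Covariates for the primary logistic model are chosen from observed imbalance and observed association with the outcome, and the randomisation strata (site, gender) are not guaranteed entry

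*Protocol article*

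**What the plan says.** The section on the analysis of primary and secondary outcomes describes a first phase that compares baseline characteristics between arms, and then gives two routes into the efficacy model.

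- Route 1, imbalance: "Baseline characteristics that are not balanced across the study arms will be advanced into regression models".
- Route 2, association with the outcome: "Characteristics that are balanced but that have an association with the outcome will also be advanced to final models to reduce error variance".

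The primary test of the intervention follows from that model: "we will use adjusted logistic regression modeling to determine successful linkage to care". Secondary outcomes are to be handled in the same way.

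The Randomization section states: "Randomization was stratified by site and gender, with blocks of varying length". The analysis section does not put either factor in the primary model. Gender appears there only in the hypothesis-generating moderator models, "with interaction between study arm and age, gender, social support scale and reason for HIV testing". Site is not named as a model term.

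**The concern.** Both routes need observed trial data, and the second needs outcomes. In a soundly randomised trial, baseline imbalance arises by chance and does not show which covariates are worth adjusting for. Adjusting for prognostic factors is good practice; the weakness is choosing them after looking. The baseline questionnaire covers demographics, emotional health, social support, barriers and competing needs, so there are many candidates and many possible final models. In logistic regression each such model estimates its own conditional effect, so the quantity reported depends on what the data happen to select.

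The strata are a second matter. An analysis normally carries the factors used to stratify randomisation. Here they enter only if one of the two data-driven routes picks them. Site is a plausible predictor of the outcome. The Sample size section says that after the McCord HIV clinic closed, participants could no longer reach the primary outcome at that site. The Discussion lists care sought elsewhere as a limitation, and the primary analysis relies on medical records. McCord contributed 1,546 of 4,903 enrollees (1,546 / 4,903 = 31.5%).

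**Working it through.** **Analysed number.** The Sample size section states "we anticipated that 22% of enrolled participants would be eligible to meet a primary outcome" and plans 4,745 enrollees: 0.22 × 4,745 = 1,043.9, so about 1,044, or 522 per arm. The allocation ratio (1:1) and a two-sided 5% level are assumptions.

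**The plan's own power figure, for context.** Inputs are "we expected 35% of HIV infected/TB negative patients in the control group to achieve the primary outcome" and "The study was originally powered (90%) to detect a 27% increase in linkage to care in the intervention arm". Read as a relative increase, 0.35 × 1.27 = 0.4445, a difference of 0.0945.

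- Pooled proportion 0.39725; null SE = √(2 × 0.39725 × 0.60275 / 522) = 0.0303.
- Alternative SE = √((0.35 × 0.65 + 0.4445 × 0.5555) / 522) = 0.0301.
- Power = Φ((0.0945 − 1.96 × 0.0303) / 0.0301) ≈ 87.8%, near the stated 90%. The rate for co-infected controls is not given; an overall control rate of 36% to 37% would give 89% to 91%.
- The same contrast as a marginal odds ratio: (0.4445 / 0.5555) / (0.35 / 0.65) = 1.486.

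No power figure changes if the covariates are fixed in advance.

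**Type I error under the rule.** Two simulations used N = 1,044 with entry at p < 0.05. The covariate numbers and effects are assumptions.

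| Null simulation | Unadjusted | Fixed model | Rule as written | Monte Carlo SE |
|---|---|---|---|---|
| A: 1,000 trials, 10 covariates, 4 prognostic | 5.9% | 5.6% (full model) | 5.7% | about 0.7 points |
| B: 3,000 trials, 20 covariates, 5 prognostic, plus 4 sites and gender | 4.1% | 4.4% (strata only) | 4.5% | about 0.4 points |

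Neither shows inflation when the rule is followed mechanically.

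**Effect estimate under the rule.** Simulation B was repeated with a true conditional odds ratio of 1.486 (1,500 trials).

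| Model | Average odds ratio | Rejection rate |
|---|---|---|
| Unadjusted | 1.43 | 79.1% |
| Strata only | 1.44 | 79.7% |
| Rule as written | 1.49 | 82.3% |

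The gap between the first and last estimates is 1.492 / 1.428 = 1.045, about 4.5% on the odds-ratio scale. This is not bias. The models estimate different conditional quantities, and the rule leaves open which one is reported.

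**Entry of the strata.** With selection term by term in simulation B, all site and gender terms entered together in 11.3% of null trials and 11.9% of trials with an effect. This depends on the assumed site and gender effects.

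**Balance of the strata in the analysed set.** Randomisation came before HIV testing, so blocking balances all enrollees, not the roughly 22% analysed. If eligibility is unrelated to arm and a stratum is exactly balanced, the variance of the arm count in a 22% subset is about 1 − 0.22 = 0.78 of its value under simple randomisation, an SD ratio of √0.78 = 0.88. Site or gender could therefore be unbalanced in the analysed set almost as readily as another covariate. Simulation B balanced the analysed set itself, so it somewhat understates entry by route 1.

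**The case against.** The strongest reply is that the consequence is small. The rule as written keeps its nominal level, and route 2 could be applied to pooled data without arm labels. That stands: the point concerns discretion and a moving target of estimation, not a demonstrated excess of false positives. A reader might infer inflation from a figure of 7.8% in simulation A, but that comes from taking the most favourable of 20 models. The best of three models in simulation B gave 5.9%. The plan calls for neither search.

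A second reply is that candidate lists and thresholds belong in a statistical analysis plan, which is not shown. That also stands, and their absence is not the complaint. The article does state the selection rule, and a plan that named its covariates in advance would have to replace that rule rather than complete it.

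Three stronger readings are not supported:

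- **Strata shut out by design.** A reader might infer that stratification prevents route 1 from selecting site and gender. The subset calculation shows otherwise, and route 2 is also open to them. Only the lack of a guarantee stands.
- **Wrong rationale.** A reader might object that covariates do not reduce error variance in a logistic model. The wording is loose but the aim is legitimate, since adjusting for prognostic covariates can gain power, as in simulation B.
- **Mismatch with the powered effect.** A reader might infer that the trial will report an odds ratio at odds with the planned 27%. The article names no effect measure, a logistic test is compatible with powering on two proportions, and the article does not say whether 27% is relative or absolute.

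**Conclusion.** The point holds in a limited form. The article fixes a rule that selects primary-model covariates from observed imbalance and observed outcome association, and it guarantees no place to the two stratification factors. The harm is a model chosen with outcomes in hand, a conditional effect that depends on that choice, and the possible omission of site although it is plausibly prognostic. In simulation the choice moved the average odds ratio from 1.43 to 1.49, with no type I error inflation. These sizes rest on assumed covariate effects, 1:1 allocation, a two-sided 5% level and entry at p < 0.05. The existence of the rule and the lack of a guarantee for the strata rest on the text alone. The change should be made, but the trial's validity does not turn on it.

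**What to change.** Replace both selection sentences with a pre-specified primary model: logistic regression on arm, site, gender and a short list of baseline covariates (for example age) named before outcomes by arm are seen. Present baseline balance descriptively, with no bearing on model content. Treat any model with other covariates as a sensitivity analysis, and apply the same model to the secondary outcomes.

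Optionally, report a standardised risk difference and risk ratio with 95% confidence intervals from the same model, and say whether the 27% is relative or absolute. This is a recommendation, not the correction of an error.

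The cost is wording only; the data are already collected. The Follow-up section describes outcome ascertainment as ongoing and blinded across arms, so at that stage the model could still be fixed in time.

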### Follow-up process

Outcomes regarding successful linkage to each step on the HIV and TB care path are ascertained through review of medical records and registers at the study sites. In addition, external sources are used, including TB outcomes from the Department of Health as well as deaths as ascertained through the South African death registry. Finally, all participants, regardless of study arm, are contacted by telephone for a follow-up questionnaire, with a minimum of 3 call attempts starting at 9 months and finishing 12 months post-enrollment. The purpose of the 9 month follow-up questionnaire is to ascertain information regarding HIV care obtained outside of the study sites, as well as changes in family composition, emotional health, social support, and barriers to care compared to enrollment.

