### Outcome measures

#### Primary outcomes

The primary outcome of the study is linkage to and retention in care assessed 9 months after enrollment for those HIV-infected individuals eligible for ART or TB treatment. The primary outcome is defined as: 1) 3 months on ART for ART-eligible HIV-infected patients, and 2) 6 months of TB treatment or 3 months on ART for HIV-infected patients co-infected with TB. Thus, for co-infected patients, a patient who links to either HIV or TB treatment is considered to have successfully reached the primary outcome. In the primary analysis, we will use data obtained from medical record review and TB treatment outcomes as documented by the Department of Health to minimize ascertainment bias in the navigator arm. HIV care received outside of the study sites will be assessed through self-report and will be used in sensitivity analyses.

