### Data collection

For HIV-related outcomes, the following data elements are collected: dates and results of HIV test, CD4 count and viral loads if available, dates of ART training, and ART initiation. Data are obtained from electronic and paper records, as well as patients’ self-report (Table 
2). Data on mortality will be obtained from clinical records, follow-up telephone contacts, and the national death registry.

**Table 2 T2:** List of study instruments, data elements and source of information

**Data collection instruments**	**Time of ascertainment**	**Data collected**	**Source**
Pre-screen checkpoints	Day of enrollment	Basic demographic information and eligibility assessment	Subject self report
Screening and baseline questionnaire	Day of enrollment	Demographic information, emotional health, social support, barriers and competing needs to care	Subject self-report
Contact information	Day of enrollment	Contact information to reach subject, including preferred language for SMS	Subject self-report
TB nurse questionnaire	Day of enrollment	TB symptoms and TB treatment history	Subject self-report
Health system navigator contact log	Day of enrollment and throughout	Perceived barriers to care and strengths to overcome barriers, time spent contacting participants	Medical record, subject self-report
Participant log	Day of enrollment and throughout	HIV test and CD4 results and retrieval, ART initiation, TB treatment dates and outcomes, date last seen	Medical record, death registry, subject self-report
9-month follow-up form	Patient telephone interview 9-mo after enrollment	HIV and TB care, demographic and clinical updates, emotional health, social support, and competing needs	Subject self-report
Study completion form	At 9-mo follow-up	Study endpoint (death, loss to follow-up, completed follow-up)	Medical record, HSN log, death registry

TB: Tuberculosis; HSN: Health system navigator.

For TB outcomes, the site of TB treatment, date of TB treatment initiation, date of TB treatment completion, date of assigned treatment outcome, and treatment outcome (cured, treatment completed, treatment defaulted, treatment failure, death) will be collected from study site TB registers as well as from the Department of Health’s TB outcomes database.

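### The planned mechanism analysis cannot show that improved social support led to linkage, because support is next measured in both arms at months 9 to 12, after qualifying treatment has begun

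*Protocol article*

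**What the plan says.** The Analysis plan section announces moderator and mediator analyses with the words "We will conduct a series of hypothesis-generating secondary analyses". The candidate factors include "enabling (social support, self-efficacy), and perceived need factors (reason for HIV testing", together with age and gender. If the intervention proves efficacious, further analyses will look at its mechanism, with this example: "whether the intervention improves social support and self-efficacy, and whether these improvements enhance linkage to care". The section adds that the results should help decide whether particular effects of the intervention, such as better self-efficacy, are central to its working.

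Table 2 (Data collection) gives the content of the enrollment questionnaire as "Demographic information, emotional health, social support, barriers and competing needs to care" and that of the 9-month form as "HIV and TB care, demographic and clinical updates, emotional health, social support, and competing needs". The Follow-up process section places the follow-up calls between months 9 and 12 and says that they capture "changes in family composition, emotional health, social support, and barriers to care compared to enrollment". Under Usual care, study staff do not contact control participants between enrollment and that call.

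On the outcome, the article states: "The primary outcome of the study is linkage to and retention in care assessed 9 months after enrollment". Success is defined as "1) 3 months on ART for ART-eligible HIV-infected patients, and 2) 6 months of TB treatment or 3 months on ART", the second part applying to patients co-infected with TB.

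**The concern.** The mechanism question has two legs: the arm changes support, and the changed support then raises linkage. The second leg needs a mediator measured after the intervention has acted and before the outcome is under way. If support is measured only once patients are already on treatment, being in care may itself have raised it. A fitted association between support and linkage would then look the same whichever way the influence ran.

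The article intends to use these results to shape later studies and to say which effects of the navigator matter. If the second leg cannot be identified, that guidance would rest on an association with no established direction, estimated in a group selected after randomization on survival and reachability.

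**Working it through.** The plan gives no figure to reproduce here. The check sets the measurement schedule against the outcome definition.

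**1. When support is measured in both arms**
- Enrollment questionnaire: completed before randomization and before HIV testing (Randomization; Enrollment procedures). It cannot carry an intervention effect.
- 9-month form: months 9 to 12 (Follow-up process; Table 2).
- In between: no study contact in usual care (Usual care).

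The plan does not name the measurement that would serve as mediator. The 9-month form is the only post-baseline candidate listed for both arms.

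**2. When a success must have started treatment**, counting time on treatment up to month 9
- ART route: 9 − 3 = month 6 at the latest.
- TB route: 9 − 6 = month 3 at the latest.

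**3. Gap between treatment start and the mediator**
- ART route: at least 9 − 6 = 3 months.
- TB route: at least 9 − 3 = 6 months.
- Each minimum grows by up to 3 months if the call is made at month 12.
- The last scheduled navigator call is at week 16: 16 × 7 / 30.44 = 3.7 months. The interview is thus at least 9 − 3.7 = 5.3 months after scheduled navigator contact ends.

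**4. Who has a value.** The form needs a participant who is alive and reached. At July 15, 2013, 1,329 of 1,899 HIV-infected participants had completed it (70.0%, matching the stated 70%). Leaving out the 114 not yet at 9 months and the 52 due gives 1,329 / (1,899 − 114 − 52) = 1,329 / 1,733 = 76.7%. The rule that counts unfound participants without records as not linked gives them an outcome value but no mediator value.

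**5. Self-efficacy.** No Table 2 row names it. In data collection it appears only as an example of a strength that navigators assess at their contacts (Research personnel training). The interaction models listed in the Analysis plan include a social support scale but no self-efficacy measure.

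**6. Illustration, on assumed effects.** 400 simulated trials were run for each effect size:
- 0.22 × 4,745 = 1,044 eligible participants, all with a support score.
- Linkage 35% against 35% × 1.27 = 44.5%, reading the stated 27% as a relative increase.
- Support had no effect on linkage; linkage raised later support by the amount shown.

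| Effect of linkage on later support | Late score associated with linkage at p < 0.05 | Odds ratio per unit of score | Mean arm difference in support |
|---|---|---|---|
| 0 | 5% | 1.00 | 0.00 SD |
| 0.2 SD | 90% | 1.22 | 0.01 SD |
| 0.3 SD | 99% | 1.34 | 0.03 SD |
| 0.5 SD | 100% | 1.65 | 0.04 SD |

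A late score would therefore usually appear to promote linkage when it does not. The median estimated share mediated stayed near zero in every row, because the induced arm difference in support is small.

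**The case against.** The strongest reply is that this work is secondary, labelled hypothesis-generating, and run only if the intervention succeeds. It fixes no mediation method, causal estimand or measurement time, and such detail is commonly left to a full protocol or SAP that is not shown. That limits the importance of the point. It does not remove it, because the article states both the schedule and the question, and no later choice of method can create an intermediate two-arm measurement.

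Four stronger readings are tempting, and the documents do not support them.
- **That temporal order is reversed in every success.** Late measurement is not late change. The 9-month form is meant to capture change since enrollment, which could have occurred during the four months of navigator contact. The outcome also includes retention up to month 9. Order cannot be established; it is not shown to be reversed.
- **That self-efficacy has no usual-care values at all.** The article calls Table 2 complete as to tools, not items. Reason for HIV testing, a planned moderator, is also missing from it. A self-efficacy item could sit inside a listed questionnaire.
- **That 77% is the completeness of the mediation data.** It is an interim count over all HIV-infected participants, whereas the primary outcome concerns those eligible for ART or TB treatment. The article's own follow-up rate is 90%, which cannot consist of completed interviews alone.
- **That the plan would yield a false mediated effect.** The simulation shows a spurious second leg, not a spurious mediated share.

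**Conclusion.** The point holds as a limit on what an exploratory analysis can conclude. On the stated schedule, the post-baseline social support value comes at least 3 months after qualifying ART began and at least 6 months after qualifying TB treatment began, and it exists only for interviewed participants. The direction between support and linkage cannot be established from it. If a two-arm self-efficacy item exists, the same limit applies, since its first post-baseline usual-care value also falls at month 9 or later.

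This rests on two assumptions: that time on treatment is counted up to month 9, and that the 9-month form is the mediator measurement, as nothing else listed fits. The simulated effect sizes are assumptions and the conclusion does not depend on them. Severity is low: the primary and other secondary outcomes are untouched, and the analysis need not be abandoned altogether.

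**What to change.** In the Analysis plan section, restrict the mechanism analysis along these lines:

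*If the intervention is efficacious, we will compare the arms, as an exploratory analysis, on change in social support from enrollment to the 9-month interview. This measure is concurrent with or later than linkage and is available only for participants who were interviewed. Any association between support and linkage will be reported as non-causal and will not be used to conclude that a particular effect accounts for the efficacy of the intervention.*

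Include self-efficacy only if a measure collected in both arms exists. In that case name it and its time points in Table 2, and apply the same restriction.

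The change is to wording only, with no new data collection. It gives up a mechanism claim that the data could not support.
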